The llluminOss® System is the first percutaneous, patient-specific, fracture stabilization system [16]. Only a small and percutaneous incision is required to insert an inflatable balloon into the medullary canal. The balloon, which spans the fracture is infused with a light curable monomer. The monomer hardens in situ by applying a visible light, resulting in a stable and patient-specific implant that provides longitudinal strength and rotational stability over the length of the implant. Early functional after-treatment without additional plaster immobilization is possible. The latter is considered the main strength of this device over non-operative treatment and conventional metal implants [16].

The IO-WRIST study is designed to determine results after treatment with IlluminOss®. Outcome will be monitored as propagated by the distal radius working groups of the International Society for Fracture Repair and the International Osteoporosis Foundation [17]. This study primarily aims to examine the effect of operative treatment using the IlluminOss® System on the DASH (Disabilities of the Arm, Shoulder, and Hand) score in elderly patients who sustained a unilateral, displaced, extra-articular distal radius fracture. Secondary objectives are to examine the effect on functional outcome, the level of pain, health-related quality of life, the time to regaining independence in activities of daily living (ADL), the resumption of work/ADL, range of motion of the wrist, the time to radiographic healing, the rate of complications with associated secondary interventions, and the costs for health care use and lost productivity.

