Radiographic evaluation will be done using routinely obtained radiographs. The degree of radial inclination, volar/dorsal tilt and ulnar variance, the amount of comminution, and the radial length will be measured directly in the digital Picture Archiving and Communication System (PACS) of the participating hospital on standard AP, lateral carporadial, or lateral wrist X-rays. Radiographs will be made using a standardized protocol; 1) for the AP radiographs, the shoulder should be held in 90° abduction, the elbow in 90° flexion, and the wrist in neutral position; 2) for the lateral X-rays, the shoulder should be held in a neutral position and the elbow in 90° flexion; 3) for the lateral carporadial radiographs, the lower arm should be positioned on a 20–25° angled wedge.

Radiographic healing and alignment of the distal radius will be evaluated using X-rays. The treating physician and two independent experts will assess the Lidström score for the repeated X-rays of the wrist blinded from the first assessment [36]. X-rays will be blinded and radiographic evaluation will be done by two experts independently. Any discrepancy will be resolved in a consensus meeting.

The following complications will be collected from the patients’ hospital records; 1) skin problems (threatened skin, necrosis); 2) Surgical site infection [37]; 3) radial nerve pathology; 4) vascular injury (hemorrhage, injury to the radial or ulna artery); 5) tendon pathology (abductor pollicis brevis/longus, extensor carpi radialis brevis/longus, extensor pollicis longus); 6) compartment syndrome; 7) secondary dislocation (loss of length, angulation, or rotation); 8) implant failure (balloon breakage); 9) non-union/pseudarthrosis (i.e., no healing or progress towards healing visible at 6 months after surgery); 10) malalignment severe enough to treat surgically; 11) CRPS type I; 12) systemic, generic or other complications.

Secondary intervention within 1 year of surgery will be collected from the patients’ hospital records. Only interventions aimed at relieving pain, treating infection, promoting fracture healing, or improving function will be recorded. They will be categorized as 1) drug treatment (oral or intraveneous antibiotics, other); 2) surgical treatment (incision and drainage, revision osteosynthesis (plate osteosynthesis, intramedullary nail or other), implant removal, other).

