### Study procedures

Patients will be followed for 1 year. Follow-up visits are scheduled at 2 weeks, 6 weeks, 3 months, 6 months, and 12 months after index surgery. These visits are standard of care for patients with a distal radius fracture. Table 1 shows an overview of the follow-up schedule, including the accepted windows around each visit.

**Table 1 Tab1:** Schedule of events

Radiographs & Events	Screening	Enrolment	Baseline	Per/Post	2 weeks	6 weeks	3 months	6 months	12 months
				surgery	(10–16 days)	(5–7 weeks)	(11–15 weeks)	(5–7 months)	(12–14 months)
X-Ray^a^	X				(optional)	X	X	X	(optional)
Screening	X								
Informed Consent		X							
Baseline Data			X						
Surgical Report Form				X					
Clinic FU					X	X	X	X	X
Range of Motion					X	X	X	X	X
DASH					X	X	X	X	X
PRWE					X	X	X	X	X
Pain (VAS)					X	X	X	X	X
SF-36					X	X	X	X	X
EQ-5D					X	X	X	X	X
ADL independence					X	X	X	X	X
Work/ADL resumption					X	X	X	X	X
Complications					X	X	X	X	X
Secondary Interventions					X	X	X	X	X
Health Care Use					X	X	X	X	X
Early Withdrawal					^b^	^b^	^b^	^b^	^b^

^a^The AP and lateral X-rays will be used for determining radiographic healing

^b^Only applicable at time of withdrawal

During these regular clinical follow-up visits, AP and lateral radiographs are made for determining radiographic healing and malalignment.

At each planned visit, the clinical investigator (or a research assistant) will document complications and secondary interventions, and will check information within the patients’ hospital files. At the last visit, all planned secondary interventions will also be recorded.

At each planned visit, a physician, clinical investigator, or research assistant will measure the range of motion of the wrist using a goniometer. In addition, patients will be requested to complete a set of questionnaires (DASH, PRWE, VAS for pain, SF-36, EQ-5D, ADL/work, health care consumption, and production loss).

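### The rule for recording secondary interventions is narrower than the complication list and the objective it serves, so the re-intervention rate can be understated

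*Protocol article*

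**What the plan says.** Four places in the protocol article bear on this variable.

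- **Background (objectives).** One secondary objective is "the rate of complications with associated secondary interventions". It sets no limit by the purpose of the intervention.
- **Outcome measures (complications).** Twelve kinds of complication are collected from hospital records, without a filter. They include skin problems, "4) vascular injury (hemorrhage, injury to the radial or ulna artery"), compartment syndrome, secondary dislocation and implant failure, and end with a catch-all item.
- **Outcome measures (secondary interventions).** Source and period are given first: "Secondary intervention within 1 year of surgery will be collected from the patients’ hospital records". The filter follows: "Only interventions aimed at relieving pain, treating infection, promoting fracture healing, or improving function will be recorded". Then come the classes: "They will be categorized as 1) drug treatment (oral or intraveneous antibiotics, other); 2) surgical treatment (incision and drainage, revision osteosynthesis", with the surgical list ending in "implant removal, other". There is no third class.
- **Study procedures.** Complications and secondary interventions are documented at each visit and checked against the hospital file, with no restatement of the filter. In addition, "At the last visit, all planned secondary interventions will also be recorded".

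Immobilisation (type and duration) is collected under Outcome measures among the characteristics that describe the treatment. A health care use questionnaire is also planned.

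**The concern.** The filter is worded as exclusive. A data manager who follows it has to ask what each intervention was for and discard those that serve none of the four purposes. Some complications in the list just before it are treated for other reasons, such as stopping bleeding or covering dead skin. Their treatment would then be missing from the variable meant to report interventions associated with complications.

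The two classes leave a second gap. A plaster or splint applied after loss of reduction is neither a drug nor an operation. The Background names early functional after-treatment without extra plaster as the main strength of the device, so a return to plaster is one of the more informative events the study could observe.

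The study is a single-arm case series of a relatively new technique. The Background itself cites a 0–50 % complication rate as a concern with intramedullary nailing. Readers will set the re-intervention rate against published figures, and a recording rule that can only remove events makes that comparison less safe.

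**Working it through.** The article gives no expected or target re-intervention rate, so there is no figure to reproduce. The check is a comparison of texts, followed by a sensitivity calculation.

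**Step 1. Each listed complication against the four aims (pain, infection, fracture healing, function).**

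| Listed complication | Does its treatment meet one of the aims? |
|---|---|
| 1 Skin problems | If infected, yes; uninfected necrosis, no |
| 2 Surgical site infection | Yes (infection) |
| 3 Radial nerve pathology | Yes (pain or function) |
| 4 Vascular injury | Not on a literal reading |
| 5 Tendon pathology | Yes (pain or function) |
| 6 Compartment syndrome | Only if improving function is read to include preserving it |
| 7 Secondary dislocation | Yes (healing or function) |
| 8 Implant failure | Usually yes; not for removal of a broken implant without symptoms |
| 9 Non-union | Yes (healing) |
| 10 Malalignment | Yes (function) |
| 11 CRPS type I | Yes (pain or function) |
| 12 Systemic or other | Depends on the event |

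Most treatments pass. The clear gaps are items 4 and 1 (uninfected). Item 6 depends on how broadly function is read.

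**Step 2. Interventions that pass the aims, against the two classes.** Closed re-reduction after secondary dislocation meets the healing or function aim and could be entered under surgical *other*. It is poorly placed, but not excluded. Plaster or splint immobilisation may meet the same aim but is neither drug nor surgical, and each *other* sits inside one of those two classes. Whether a site enters it at all is left to local reading.

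**Step 3. Is the gap closed elsewhere?** Immobilisation is recorded as a descriptive characteristic. The article does not link it to a complication or count it as a secondary intervention. The health care use questionnaire feeds the cost analysis. Either might let someone reconstruct an event, but neither enters the secondary-intervention rate as described.

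**Step 4. Direction.** The filter and the missing class can remove interventions and cannot add any. Through this route the count can only be too low.

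**Step 5. What one missed patient is worth.** Inputs from Sample size calculation: 50 enrolled, 38 needed after losses.

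- 1/50 = 2.0 percentage points; 1/38 = 2.6 percentage points.
- Assumed range of 1 to 3 patients whose only re-intervention is filtered out: 1/50 to 3/50 = 2 to 6 points; 1/38 to 3/38 = 2.6 to 7.9 points.
- Illustration with two missed patients (assumed): a true 5/50 = 10 % (exact 95 % CI 3.3 to 21.8) would be reported as 3/50 = 6 % (1.3 to 16.5).

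These numbers show only the scale. The documents do not say how often such events are expected.

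**The case against.** The case on the other side is substantial, and much of it stands.

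- **The events are not lost from the safety data.** A reader might infer that the rule removes some of the most serious events. It does not. Vascular injury, compartment syndrome, skin necrosis and implant failure are all collected as complications without a filter. At most, the treatment is missing from a second variable.
- **Most re-interventions pass.** Step 1 confirms this. Improving function can also be read to cover compartment release and arterial repair. That reading is reasonable, but four hospitals may not all adopt it, and the count would then depend on the site.
- **The period is defined.** The 12–14 month window for the last visit might suggest that complications have no stated end, or that observation time differs between patients by up to (14 − 12)/12 = 17 %. The documents do not support either. The Abstract and Study procedures set follow-up at 1 year after surgery, and secondary interventions are limited to 1 year whatever the visit date. The window applies to the visit.
- **The weight is modest.** This is one of eleven secondary outcomes in a descriptive study, and no decision rule rests on it. This stands.
- **A journal article condenses.** Form definitions are often left to the full protocol. Here, however, the article states an exclusive rule and two classes. The problem is what that rule says, not that detail is absent.

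**Conclusion.** The point holds in a limited form. The recording rule and its two classes do not match the complication list in the same section or the objective in the Background. Read literally, they omit interventions for haemorrhage or arterial injury and for uninfected skin necrosis, possibly those for compartment syndrome, and they give plaster or splint after secondary dislocation no class.

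The secondary-intervention rate *can* therefore be understated, and any such error would flatter the device. It is tempting to say that the rate *is* understated. That is not shown: the article states no rate and no expected frequency of the affected events, and the effect requires both that such events occur and that sites read the rule strictly. The size is unknown, at 2.0 points per missed patient with 50 in the denominator (2.6 with 38).

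A smaller point belongs with it. Interventions only planned at the last visit are recorded, but the article does not say whether they enter the rate. Mixing them with performed interventions would push the count the other way.

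**What to change.** Replace the filter sentence and extend the classes:

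1. Record every unplanned intervention on the affected wrist or forearm, and every intervention linked to a recorded complication, within 1 year of surgery and whatever its aim, with its date and the linked complication.
2. Add a third class, non-operative, for example closed re-reduction, plaster or splint.
3. Report interventions only planned at the last visit separately from those performed.

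This changes what is recorded and leaves patient management untouched. It brings Outcome measures into line with the Background objective and with Study procedures. The cost is one reworded sentence and one category on the form, with no extra visits. The reported rate may become slightly less favourable.

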### Study procedures

Patients will be followed for 1 year. Follow-up visits are scheduled at 2 weeks, 6 weeks, 3 months, 6 months, and 12 months after index surgery. These visits are standard of care for patients with a distal radius fracture. Table 1 shows an overview of the follow-up schedule, including the accepted windows around each visit.

**Table 1 Tab1:** Schedule of events

Radiographs & Events	Screening	Enrolment	Baseline	Per/Post	2 weeks	6 weeks	3 months	6 months	12 months
				surgery	(10–16 days)	(5–7 weeks)	(11–15 weeks)	(5–7 months)	(12–14 months)
X-Ray^a^	X				(optional)	X	X	X	(optional)
Screening	X								
Informed Consent		X							
Baseline Data			X						
Surgical Report Form				X					
Clinic FU					X	X	X	X	X
Range of Motion					X	X	X	X	X
DASH					X	X	X	X	X
PRWE					X	X	X	X	X
Pain (VAS)					X	X	X	X	X
SF-36					X	X	X	X	X
EQ-5D					X	X	X	X	X
ADL independence					X	X	X	X	X
Work/ADL resumption					X	X	X	X	X
Complications					X	X	X	X	X
Secondary Interventions					X	X	X	X	X
Health Care Use					X	X	X	X	X
Early Withdrawal					^b^	^b^	^b^	^b^	^b^

^a^The AP and lateral X-rays will be used for determining radiographic healing

^b^Only applicable at time of withdrawal

During these regular clinical follow-up visits, AP and lateral radiographs are made for determining radiographic healing and malalignment.

At each planned visit, the clinical investigator (or a research assistant) will document complications and secondary interventions, and will check information within the patients’ hospital files. At the last visit, all planned secondary interventions will also be recorded.

At each planned visit, a physician, clinical investigator, or research assistant will measure the range of motion of the wrist using a goniometer. In addition, patients will be requested to complete a set of questionnaires (DASH, PRWE, VAS for pain, SF-36, EQ-5D, ADL/work, health care consumption, and production loss).

### Sample size calculation

For case series, a generally accepted assumption is that introducing and implementing a (relatively new) surgical technique requires 30 patients [39]. A formal sample size calculation for this study is based on the DASH score (primary outcome measure). The minimal important change for the DASH score is 10 points [19]. Based on literature data we expect a mean DASH of 23 (SD 19) in non-operatively treated patients [40, 41]. In order to detect a 10-point improvement (mean 13, SD 10) in patients treated with IlluminOss® with a two-sided α of 0.05 and a 90 % power (β = 0.10), at least 38 patients are needed. Anticipating 10–15 % loss to FU and 10 % mortality, 50 patients will be enrolled.

### Statistical analysis

The Statistical Package for the Social Sciences (SPSS) version 21 or higher (SPSS, Chicago, Ill., USA) will be used for statistical analysis. The STrengthening the Reporting of OBservational studies in Epidemiology (STROBE) guidelines will apply to data reporting. If necessary, missing values will be replaced using multiple imputation following the predictive mean matching method, using ten imputations. The Shapiro-Wilk test will be used for testing normality of continuous data. All statistical tests will be two-sided, and a p-value <0.05 will be used as threshold of statistical significance.

Descriptive analysis will be performed in order to report baseline and outcome data. Data will be reported as mean with SD (continuous, parametric data), as median with first and third quartile (continuous, non-parametric data), or as number with frequency (categorical data). A Wilcoxon Signed Rank test will be applied for comparing continuous outcome scores at 1 year with those at their first measurement.

Depending on the variability of covariates, multivariable analysis may be performed. A linear mixed-effects regression model will be made to model the relation between specific covariates and the outcome measures that are recorded repeatedly (i.e., DASH and other PROMs). This multilevel model will include fixed effects for covariates like involvement of the dominant side, gender, and age if deemed necessary. These confounders will be selected based upon literature data and by eyeballing the descriptive statistics. The beta values will be reported with their 95 % confidence interval and p-value. Estimated marginal mean will be computed and reported per follow up moment.

For the continuous data determined only once (e.g., time to radiographic healing), a multivariable linear regression model may be developed, with the outcome measure as dependent variable. Potentially confounding variables will be entered as covariate. Beta values will be reported with 95 % confidence interval and p-value.

For the categorical data, a multivariable logistic regression model will be developed, with the outcome measure as dependent variable. Potentially confounding variables will be entered as covariate. Odds ratio’s will be reported with 95 % confidence interval and p-value.

The economic evaluation will include costs for health care as well as for lost productivity. Direct and indirect, medical and non-medical cost will be measured as indicated in the Dutch guidelines for economic evaluations, using standard, published cost prices where possible [42]. Costs for lost productivity will also be calculated.

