## Methods/design

### Study design

The IO-Wrist study is a multicenter, prospective, observational study (i.e., case series). As the intervention studied is a relatively new technique and there is a lack of published evidence a case series was preferred over a study comparing the intervention with a control group. The following four hospitals in The Netherlands will participate: 1) Albert Schweitzer Hospital, Dordrecht; 2) Amphia Hospital, Breda; 3) Deventer Hospital, Deventer; and 4) Erasmus MC, Rotterdam. The study is registered at the Netherlands Trial Register (NTR5457), registration date September 29, 2015.

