### Outcome measures

The primary outcome measure is the Disabilities of the Arm, Shoulder and Hand outcome measure (DASH). This questionnaire is validated and is completed by patients. It reflects the disability experienced by patients with an upper-limb disorder, and is used for monitoring changes in symptoms and function over time [19–22]. The DASH disability/symptom score is the sum of responses to 30 items (scored 1-5), which test a) the degree of difficulty in performing a variety of physical activities (21 items); b) the severity of pain, activity-related pain, tingling, weakness, and stiffness (5 items); and c) the effect on social activities, work, sleep, and self-image (4 items). The total score ranges from zero (no disability) to 100 points (severe disability). At least 27 of the 30 items must be completed. A validated Dutch version is available [23]. The DASH optional modules for Work and high performance Sport/Music (both 4 items, scored 1–5) will also be completed. The score can only be calculated if all items are completed.

The secondary outcome measures are:Patient-Rated Wrist Evaluation (PRWE)Pain level at both sides (VAS)Health-related quality of life: Short Form-36 (SF-36) and EuroQoL-5D (EQ-5D)Time to regaining independence in Activities of Daily Living (ADL)Resumption of work and other activities of daily livingRange of Motion of the wrist at both sidesRadiographic evaluationComplicationsSecondary interventionsHealth care consumption with associated costsProductivity loss with associated costs

The Patient-Rated Wrist Evaluation (PRWE) measures functional outcome in patients diagnosed with a distal radius fracture [24]. In this 15-item questionnaire, patients are asked to rate the level of pain and disability in their wrist from zero (no pain/difficulty) to 10 (worst pain/unable to do) [25, 26]. The PRWE consists of a 5-item Pain subscale, a 6-item Specific Activities subscale, and a 4-item Usual Activities subscale. Responses to the individual subscales are summed. The total score for wrist pain and disability (100 points) is computed by dividing the sum of the ten functional items by two and adding that subtotal (50 points) to the score for the pain subscale (50 points). This provides a score that ranges from 0 (no pain or disability) to 100 (high level of pain or disability). A validated Dutch version is available [27].

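### The DASH contrast that sizes the study (13 versus a literature mean of 23) has no matching analysis or time point; the one planned test of the scores measures change from 2 weeks after surgery to 1 year

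*Protocol article*

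**What the plan says.** The Background gives the primary aim in causal terms: "This study primarily aims to examine the effect of operative treatment" with IlluminOss on the DASH score. The design is a case series with no control group.

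The Sample size calculation supplies an external comparator: "Based on literature data we expect a mean DASH of 23 (SD 19) in non-operatively treated patients". It continues "In order to detect a 10-point improvement (mean 13, SD 10) in patients treated with IlluminOss" and "with a two-sided α of 0.05 and a 90 % power (β = 0.10), at least 38 patients are needed". Fifty patients are to be enrolled to allow for loss and death. No visit is attached to the 13 or the 23, and the Outcome measures section names DASH as primary without a time point.

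The Statistical analysis section sets a two-sided 0.05 threshold. Within its descriptive paragraph it states "A Wilcoxon Signed Rank test will be applied for comparing continuous outcome scores at 1 year with those at their first measurement". It then allows mixed-effects, linear and logistic regression with p-values for coefficients or odds ratios, and lists estimated marginal means for each follow-up visit. The value 23 does not appear there, nor does any other external value.

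On timing, Study procedures says "Follow-up visits are scheduled at 2 weeks, 6 weeks, 3 months, 6 months, and 12 months after index surgery". Table 1 shows DASH at those five visits and none at screening, enrolment or baseline.

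The Discussion mentions comparing results with published non-operative data but gives no method. It expects similar outcome at 1 year and an advantage on DASH only up to 6 months.

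**The concern.** A formal power calculation commits the study to a hypothesis, here that mean DASH after IlluminOss is lower than 23. Followed as written, the analysis never confronts that hypothesis. What it does test is whether scores at 1 year differ from scores about 2 weeks after surgery. With one arm and no score from before treatment, that difference contains normal healing, rehabilitation and any device effect, with no means of separating them.

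At stake is how the main result will be read. A small p-value for the change can arise when patients do no better than the non-operative benchmark, yet it would be the only p-value on the primary outcome's level or change in a report whose stated aim is the effect of the operation. The Wilcoxon test also uses 1 year, the visit at which the authors expect no advantage over non-operative care.

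**Working it through.** **1. Which test does the stated 38 belong to?**

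Inputs from the Sample size calculation: difference 23 − 13 = 10, SD 19 (benchmark) and SD 10 (IlluminOss), two-sided α 0.05, power 90%. Then z(0.975) + z(0.90) = 1.9600 + 1.2816 = 3.2415.

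- One sample against a fixed 23, SD 19: n = (19 × 3.2415 / 10)² = 37.9, rounded up to 38. This reproduces the plan's figure. The t version gives 40.
- One sample, SD 10: (10 × 3.2415 / 10)² = 10.5, so 11.
- Two independent groups, SDs 19 and 10: pooled SD = √((361 + 100)/2) = 15.18, giving 49 per group.
- Paired, SDs 19 and 10, assumed correlation 0 / 0.3 / 0.5 / 0.7: 49 / 37 / 29 / 21.

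The direct match is a one-sample test against 23 with SD 19. A paired reading comes near 38 only if a correlation of about 0.3 is assumed, and the article gives none. It would also need 23 to be the patients' own earlier mean, whereas the article assigns it to other patients. Enrolment is consistent too: 38 / (0.90 × 0.85) = 49.7, so 50.

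**2. Is that test in the analysis section?**

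| Planned item | Question it answers | Uses 23? |
|---|---|---|
| Shapiro-Wilk | Are the data normal? | No |
| Wilcoxon signed rank | Do scores change from first measurement to 1 year? | No |
| Mixed, linear and logistic regression | Are covariates related to outcome? | No |
| Estimated marginal means per visit | What is the mean at each visit? | No, although they could be set against it |

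**3. What can the Wilcoxon test show when there is no gain over the benchmark?**

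Set the 1-year mean at 23 (SD 19) with 38 pairs. The 2-week mean, its SD and the correlation are not in the article and are assumed. Scores are kept within 0 to 100.

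| Assumed 2-week mean | A: skewed (gamma) 1-year scores, 2-week SD 20, correlation 0.2 / 0.5 | B: normal scores, SD 19 at both visits, correlation 0 / 0.5 |
|---|---|---|
| 30 | 51% / 69% | 32% / 56% |
| 35 | 88% / 97% | not run |
| 40 | not run | 95% / >99.9% |
| 45 | 100% / 100% | not run |
| 50 | not run | 100% / 100% |
| 55 | 100% / 100% | not run |

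Entries are the share of simulated studies with p < 0.05 (1,000 per setting in A, 2,000 in B).

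**4. Would the existing sample size support the missing comparison?**

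For a true mean of 13 tested against a fixed 23 with n = 38, power is 90.1% (z) or 88.5% (t) at SD 19, and over 99.9% at SD 10.

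**The case against.** The strongest reply is that the study calls itself a case series, says it will report descriptively, and explains why a controlled comparison was not attempted. The Wilcoxon test sits in the descriptive paragraph, applies to every continuous score, and is never called the primary analysis. In that role a change from 2 weeks to 1 year is a fair description of recovery. The lack of a preoperative score follows from a design that allows inclusion as late as the 2-week visit. Marginal means per visit are already listed, and the Discussion foresees setting results beside published data.

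Much of this stands, and it rules out several stronger readings that a reader might infer:

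- That the Wilcoxon test is the only hypothesis test in the plan. It is not: a normality test and regression p-values are planned as well. It is the only planned test of level or change in the outcome scores.
- That the plan presents this test as proof of a device effect. The article attaches no such claim to it.
- That significance is certain whatever the device does. This depends on 2-week values that the article does not give; at an assumed mean of 30 the rate is roughly 30 to 70%.
- That a missed 2-week form is a serious flaw because the first measurement would then vary between patients. Table 1 fixes the first DASH at 2 weeks and multiple imputation is foreseen, so this is minor.

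What the reply does not answer is the mismatch itself. The article states a powered, two-sided hypothesis against 23 and then describes an analysis that leaves it untested. This is not detail left to a fuller document: both halves are in the article and do not fit together. The marginal means are no rescue as written, because multivariable analysis is optional and no comparison with 23 is attached to it.

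**Conclusion.** The point holds in this form: the contrast used for sizing has neither a planned analysis nor a time point, and the one planned test of the scores answers a different question. That rests on the article's text and on the reproduction of 38 as a one-sample calculation. The figure of 38 is not an arithmetic error under that reading, although the SD that yields it is the benchmark's 19 and not the 10 expected for IlluminOss patients.

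The size of the interpretive risk is conditional. If the 2-week mean DASH is about 35 to 40 or more, the Wilcoxon test would be significant in 88% or more of studies with no gain over the benchmark; at 30 the range is 32 to 69%.

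The missing time point is part of the same problem. If 23 is a 1-year value, the Discussion's expectation of similar outcome at 1 year contradicts the 10-point gain that sized the study. If it belongs to an earlier visit, the sized contrast and the visit used in the Wilcoxon test do not coincide.

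**What to change.** 1. Name the primary DASH time point. Reconcile it with the Discussion's expectation of benefit only until 6 months, and with the follow-up time to which the literature value of 23 applies.
2. Make the primary analysis the mean DASH at that visit: the estimated marginal mean from a mixed model that will be fitted, not one that may be, with visit as a categorical effect. Report it with a 95% CI against 23. An upper limit below 23 corresponds to the two-sided 0.05 test for which the study was sized.
3. Report the estimated difference from 23 beside the 10-point minimal important change. Do not require the upper limit to be at or below 13. If the true mean is the planned 13, that would happen in only about 2.5% of studies: with n = 38 the upper limit averages about 13 + 2.03 × 10/√38 = 16 at SD 10, or 13 + 2.03 × 19/√38 = 19 at SD 19.
4. State that 23 is a historical value with its own sampling error, so the contrast is uncontrolled and does not isolate a device effect either.
5. Keep the 1-year versus 2-week Wilcoxon test as a description of recovery only.

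Alternatively, drop the benchmark hypothesis and justify the number of patients by the precision of the mean DASH. From the arithmetic in item 3, the 95% CI half-width with 38 patients is about 3 points at SD 10 and 6 at SD 19.

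The cost is wording. No visits or patients are added, since 38 evaluable patients give about 88 to 90% power against 23 at SD 19 if the true mean is 13. The small downside is a primary result that may look less favourable and is openly historically controlled.
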